#### Contextual determinants (Aim 2)

Contextual determinants are levels of the system, organization, or the individuals working within the organization that influence implementation outcomes. In addition, there are physical characteristics of the organization itself, such as size, location (urban/rural), or level of care that may influence implementation outcomes. We selected three commonly used measures associated with two major contextual determinant frameworks: Consolidated Framework for Implementation Research (CFIR) and the Exploration, Preparation, Implementation and Sustainment (EPIS) [42].

In this study, we developed the contextual determinant inventory (CDI) following the CFIR, EPIS, and Health Equity Implementation Framework [61]. The CDI’s 42 items are organized in four levels: system, program, staff, and patient. The rating scale ranges from Strongly Disagree to Strongly Agree and includes a Does not apply option. A 43rd item is an open-ended question asking about other contextual determinants that may affect implementation but were not included in the CDI. Scores can be tallied overall, for the 42 items, by individual items, or by dimension. Like the IMAT, the CDI is a team-assessment measure completed by key staff in MOUD implementation.

Based on the EPIS, the Implementation Climate Scale (ICS) includes 6 subscales and 18 items scored on a 5-point scale from 0 – not at all, to 4 – very great extent [62]. The Implementation Leadership Scale (ILS) is composed of 12 items divided into four subscales [63, 64]. The items are rated on a 5-point scale from 0 – not at all, to 4 – very great extent. The ICS and ILS are surveys completed by at least 5 staff members at each organization. Each of these measures will be collected at baseline, at the 4 implementation intervals, and at any 1-year post-implementation support.

#### Implementation strategy participation, fidelity, and costs (Aim 3)

Advanced measures of implementation strategy participation, fidelity, and cost are the key study features that increase precision and scientific rigor. We will use four measures to detail the contents of the “black box” of implementation strategies: NIATx Fidelity Scale, Stages of Implementation Completion (SIC), Costs of Implementing New Strategies (COINS), and an Extended CONSORT diagram to describe how programs stepped through the different implementation strategies.

The *NIATx Fidelity Scale* is a 19-item observational measure of adherence to the NIATx model, rating activities on a 5-point scale from *1-No evidence to 5-Extensive evidence*. Scoring reflects information obtained from IF and EF perspectives using a composite of interviews, review of walk-through results, change project forms, EF or IF notes, and sustainability plans. The research team will monitor NIATx delivery and formally assesses fidelity by utilizing an online data collection tool with input from external facilitators (e.g., coaches) after each strategy of the active NIATx-IF and NIATx-EF implementation phase. Where significant deviations are identified at the first fidelity check, corrective adjustments can be made.

The SITT-MAT Adaptative Implementation Strategy Design involves four strategies (EMF, NIATx/MAT Academy, NIATx-EF, NIATx-IF) and five possible pathways for programs that participate. Therefore, the current project will include assessments of strategy adherence across the five possible paths using the *Stages of Implementation Completion (SIC)* and the resources required using the *Cost of Implementing New strategies (COINS)*.

The SIC is an 8-stage assessment tool that is psychometrically valid and reliable [65–69]. The SIC is designed to measure and compare implementation strategies for scaling up proven interventions [51]. Stages range from engagement (Stage 1) to achievement of program delivery with competency (Stage 8) [67]. SIC data include a log of activities that operationalize the implementation process necessary to move toward successful program start-up and sustainment and their completion dates. Two scores are calculated for each SIC stage. The *Proportion* score calculates the proportion of key activities completed within a stage. The *Duration* score is calculated by the date of entry through the date of the final activity completed. The Duration score can account for activities not completed sequentially and for being in multiple stages at a given time. A third *Final Stage* score indicates the final stage achieved in the implementation process (Stages 1–8). The SIC has been adapted or customized for multiple evidence-based practices (EBPs) [70–75] and evaluated across different system settings [51, 76, 77].

The SIC has the ingredients of a map for costing implementation strategies. As a companion to the SIC, The Cost of Implementing New Strategies (COINS) was developed as a cost mapping procedure to collect implementation resource information and to assist in disentangling implementation from intervention costs. Since staff spend a considerable number of hours involved in implementation activities, the COINs was developed to calculate the fees, expenses, and person hours necessary to complete each stage [78]. Its application will identify cost and resources differences between implementation strategies for the proposed cost analyses in Aim 3 [79, 80].

For the SITT-MAT study, the SIC and COINS will be customized using a standardized adaptation approach [72]. Each of the five possible paths of implementation strategies will be operationalized. This will allow for a comparison of implementation strategy approaches and costs across programs and possible paths. If a program stops implementation strategy support at any step, their SIC measurement will discontinue. If the next step implementation strategy is initiated, a new SIC will be used to monitor the programs’ associated efforts and costs. Online data collection systems will be created to continuously collect information about the activities and costs necessary to complete the SIC and COINS.

### Data analysis

#### Specific aim 1

The analysis for Aim 1 will compare the randomized NIATx-IF versus NIATx-EF on our primary implementation outcome of the proportion of MOUD patients receiving medication within 72 h of OUD diagnosis over time. For the changes over time in the proportion of patients initiating MOUD within 72 h of diagnosis, we expect 48 new patients with OUD each quarter for each of the 54 expected sites that are randomized to either IF or EF. We will use 2-level latent growth models of 10 quarters of outcome data with individual-level binary outcomes of MOUD within 72 h. Specifically, we assume that the number of patients who start MOUD at the *i*th site and *t*th time point, *i* = 1,…,54 and *t* = 1,…,10, are all independent binomials with success probability pit on 48 individual patient trials. Here logit (pit) = ai + bi t + εit with random intercepts ai and random slopes bi = β0 + β1 Fi + εi and Fi is the indicator of facilitator condition and the effect is tested through coefficient β1.

To account for multiple comparisons in secondary analyses, we will use a false discovery rate to reflect how many subscales are assessed for each measure. In addition, we will use exploratory graphical measures, such as empirical *q*-*q* plots, to compare all the subscales’ differences by intervention condition [81]. For the analyses of the stagewise implementation to target outcomes, we will assess the degree to which all the sites eventually achieve the criterion. This criterion is defined as an IMAT Total Score ≥ 3, the presence of an integrated prescriber for MAT, and at least 50% of patients with OUD on MOUD. This is accounted for by computing the proportion of the study sites that achieve criterion in their respective phase and computing two different proportions, one for each facilitation condition, much the same way that SMART designs are evaluated for overall optimal impact.

#### Specific aim 2

We will conduct mediation and moderation analyses in the randomized trial component. For the moderation analysis, we will assess whether the size of the patient population (i.e., bed size or annual admissions) moderates the impact by testing the interaction term of size by implementation strategy. A core mediator of access to MOUD within 72-h of OUD diagnosis is the Phase 3 IMAT score which will be used to assess whether and how rapidly implementation occurs. For moderation, we will include Phase 3 IMAT score as an intermediary outcome and assess the indirect effect of the implementation strategy condition affecting the delivery of services through Phase 3 IMAT score on the MOUD rate. We will use the “product of coefficients” method for analyzing impact with a Poisson model for the MOUD rate outcome as we have shown this method is superior to the “difference of coefficients” [82]. Contextual determinant measures (CDI, ICS, ILS) and the organizations’ characteristics will also be examined for mediation and moderation of implementation outcomes and in response to specific strategies.

#### Specific aim 3

We will estimate the costs for each of the five implementation strategy paths. We will focus on obtaining a complete picture of relevant variable costs for the implementation strategies based on staff time and other variable cost such as supplies, staff travel, related contracts, ongoing IT costs, and staff space [83]. Using the activities, we will estimate labor costs using wage rates from the US Bureau of Labor Statistics that allow us to estimate costs for the local site, as well as a national average. Both are useful for replication. Local costs are informative to Washington State, while the national average is helpful for other systems or organizations interested in replicating this effort.

The costs will reflect the amount spent on implementation activities per time period. There is no empirical evidence on the optimal period of time, but there is a tension because narrow time periods require more data collection. While wider time periods require less data collection efforts, they yield cost estimates that are less precise (and perhaps less accurate). We will use quarters (90 days) as the time period. We will track implementation activities for the major organizational actors and external team members (e.g., EFs) using the COINS. We will estimate costs for the five implementation strategy paths and the stages of implementation, as measured by the SIC. Our method will allow us to document effort as well as the time it takes to move through the stages of implementation.

We will then use multivariate regression models to analyze effort and costs; although these outcomes are linked, often organizations want to understand the effect on each. For the cost analyses, we will consider different models and choose the best fitting model based upon the modified Park test, Box-Cox regression, and Hosmer and Lemeshow tests [84]. We will then link the cost per strategy to the outcomes measured in specific aim 1 (i.e., “implementation cost-effectiveness” not a cost-effectiveness analysis.

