**Fig. 3 Fig3:**
[figure not shown]
SITT-MAT adaptative implementation strategy design

**Table 2 Tab2:** SITT-MAT implementation strategies

**Strategy**	**Description**
**Enhanced monitoring and feedback (EMF)**	All participants will receive EMF initially and throughout the course of the active implementation phase of the study. EMF consists of the following: • Performance data gathered and reported by the program for reach and adoption on a quarterly basis • Reach, adoption, and effectiveness data summaries and IMAT results for each program, and, in comparison to the entire sample, will be reflected back to clinical leaders and staff members, via dashboards
**NIATx/MAT academy**	Two-day workshop: • Day 1 – Provide participating programs with rationale, clinical practice, and program integration with MOUD. [name] and regional MOUD expert leader prescribers will present clinical aspects of MOUD, integrating MOUD into culture and workflow, and managing complex situations • Day 2 – Provide participating programs with an overview of NIATx principles and tools. [name], who has used the NIATx academy to train over 1000 individuals, will provide participants with the critical skills (e.g., building change teams, conducting walkthroughs) and tools (e.g., process flow charts, nominal group technique) needed to implement rapid cycle Plan-Do-Study-Act (PDSA) process improvement
**NIATx-internal facilitation (NIATx-IF)**	Internal facilitators will receive training on how to provide coaching within their organization. For 9 months, they will do the following: • Support teams to harness resources toward systemic change and improvement • Employ a range of concepts and tools to provide individualized support to teams • Help teams to practice and hone their skills to optimize performance • Focus on team relationships and communications • Participate in group coaching calls involving IFs from other NIATx-IF programs and moderated by NIATx expert to discuss common change-related issues, progress, and successful tactics

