All programs that do not achieve or sustain target outcome criteria by the end of Phase 3 (12 months from baseline) will be randomized to either of the remaining two implementation strategies—NIATx Internal Facilitation (NIATx-IF) and NIATx External Facilitation (NIATx-EF). The NIATx-IF strategy features an internal change leader (employee) who will help other staff gain skills and efficacy to implement changes and address barriers in attitude and beliefs. Thus, determinants at the individual and organizational levels are the focus of the NIATx-IF implementation strategy (Fig. 2). NIATx-EF is an evidence-based implementation strategy that is widely used and studied [45]. NIATx-EF features an external expert or coach. The coach leverages their expertise and knowledge to guide staff in implementing changes, help employees gain confidence and skills, and address potential obstacles including stigma and attitudes [22, 48]. For the same reasons as NIATx-IF, NIATx-EF is tailored to issues at the organization and individual levels. IF and EF models have been systematically studied and compared [46, 49, 50]. Although there is evidence for both IF and EF, with better outcomes for EF, the cost for EF is likely greater than for IF [49]. Using the procedures employed in a previous implementation trial, we will balance the two groups before randomization [51]. We will then use a randomized cluster group trial design to compare NIATx-IF to NIATx-EF.

In our study design, programs that “graduate” to the sustainment/follow-up arm but then fail to maintain the criteria of success for two consecutive quarters will have two opportunities to rejoin the active implementation strategy phases (Fig. 3). The first opportunity where a program on Path 1 could re-enter is at the end of Phase 3 if they do not sustain improvements after receiving the EMF strategy. The second opportunity for a program on Path 2 to re-enter would be at the end of Phase 4 if they do not sustain improvements after receipt of the EMF and NIATx/MAT Academy implementation strategies. There are thus five possible paths a program might take in this study. Months in the active implementation stage range from 6 (Path 1) to 30 (Path 5). The sustainment period ranges from 12 months (Path 5) to 36 months (Path 1). The path followed by a program depends on when it meets (and sustains) implementation targets.

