Implementation quality will be measured using the Integrating Medications for Addiction Treatment (IMAT) Index. The IMAT is a newer measure built upon the same framework and methodology as its widely adopted predecessors [26, 56, 57]. The IMAT, comprised of 45 items clustered into seven dimensions (Additional File 2), integrates MOUD guidelines, expert consensus recommendations, the OUD care cascade, and best practice information into a team-assessment benchmark measure of current and future state MOUD capability and practice [58]. Confirmatory factor analyses support the validity of the IMAT Total Score, as well as the validity of each dimension. Reliability scores for each dimension range between 0.70 and 0.95. The IMAT has been useful to systems, organizations, and teams as an objective measure of current state MOUD practice and as a blueprint for measurable practice change. Like the DDCAT, the IMAT is transparent in depicting what is needed to score a 3 or 5 for practices seeking to improve implementation quality.

Three primary outcomes-Reach, Adoption, and Implementation (IMAT) serve as implementation targets to determine the stagewise path of participating organizations. A program will meet the SITT-MAT adaptative assessment criteria if (1) greater than or equal to 50% of their patients with OUD are receiving a MOUD (Reach), (2) the program has an integrated MOUD prescriber who is employed or contracted by the program (Adoption), and (3) the IMAT Total Score is greater than or equal to 3 (Implementation). By including a measure of intervention quality (IMAT), our study will overcome the threat of implementation without fidelity being no better or even harmful [59, 60]. The Reach and Adoption primary outcome measures will be gathered at baseline and quarterly for the duration of the trial, to the end of the sustainment phase and the IMAT-SC will be assessed at baseline and at the end of each phase (Fig. 3).

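### The printed primary model is valid but uses no pre-randomisation outcome data and no balancing factors; adding them could gain power, by an amount the protocol does not fix

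*Protocol article*

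**What the plan says.** Data analysis, Specific aim 1, writes the model out. It states "We will use 2-level latent growth models of 10 quarters of outcome data" and that the site-by-quarter counts "are all independent binomials with success probability pit on 48 individual patient trials". The linear predictor is logit(p_it) = a_i + b_i t + ε_it, "with random intercepts ai and random slopes bi", where b_i = β0 + β1 F_i + ε_i and F_i indicates the facilitation arm. The test is on β1. The fixed part is therefore time and time by arm. There is no arm term on the intercept, no covariate and no term for earlier quarters.

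Power calculations starts both arms at 20% at randomisation. Implementation strategies places randomisation at the end of Phase 3, 12 months from baseline. The same section says: "Using the procedures employed in a previous implementation trial, we will balance the two groups before randomization". The balancing factors are not named.

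On earlier data, Implementation outcomes (Aim 1) says: "The Reach and Adoption primary outcome measures will be gathered at baseline and quarterly for the duration of the trial". Table 2 gives enhanced monitoring and feedback to every program from the start, and the feedback includes "Reach, adoption, and effectiveness data summaries and IMAT results for each program". Table 3 counts 72-hour access under effectiveness and describes quarterly monitoring of the primary outcomes. IMAT is scored at baseline and at the end of each phase.

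**The concern.** Each randomised site will have about four quarters of history before facilitation starts. With 54 expected sites, about 27 per arm, variation between sites limits the precision of the slope comparison. A site's own history is an inexpensive way to remove part of that variation. The printed model instead estimates each site's starting level only from quarters after randomisation.

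The arms are also balanced by design, and an analysis that leaves out prognostic balancing factors tends to give a standard error that is too wide. At stake is precision, not bias. Power is stated as 80% for 54 sites, and the protocol itself allows for 49 on the continuous outcomes, so there is little slack.

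**Working it through.** **1. Which quarters the model covers.** Path 5 has 30 active plus 12 sustainment months, and Path 1 has 6 plus 36. Both total 42 months. Randomisation is at month 12, and (42 − 12)/3 = 10 quarters. The 10 modelled quarters are thus the whole post-randomisation period, and the earlier 12/3 = 4 quarters are outside the model.

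**2. The plan's own figure.** The inputs are 54 sites (27 per arm, 1:1 assumed), 48 patients per site-quarter, 20% at the start, and 54% versus 45% in the last quarter. Type I error is 5%; two-sided is assumed.

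- Effect on the logit scale: ln(0.54/0.46) − ln(0.45/0.55) = 0.361. Over 9 intervals this is 0.361/9 = 0.0401 per quarter.
- 80% power requires SE(β1) = 0.0401/(1.960 + 0.842) = 0.0143.

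Variation between sites is described only as moderate, so the 80% cannot be recomputed. It is attainable: intercept SD 0.5, site-by-quarter SD 0.2 and slope SD 0.036 per quarter give it.

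**3. Adding four pre-randomisation quarters.** The variance of β1 comes from generalised least squares on the logit scale, with binomial variance 1/[m p(1−p)] per site-quarter, m = 48 unless shown. The slope SD is calibrated so that the printed model gives 80%. All variance components are assumptions. The shift columns let each site's level move by a random amount (SD in logits) at randomisation; the other two carry it over unchanged.

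| Intercept SD | Site-quarter SD | Slope SD | Printed | No shift | No shift, m = 12 in pre-quarters | Shift 0.3 | Shift 0.5 | Shift 0.8 |
|---|---|---|---|---|---|---|---|---|
| 0.3 | 0.2 | 0.039 | 80% | 85.1% | 82.2% | 82.3% | 81.2% | 80.5% |
| 0.5 | 0.2 | 0.036 | 80% | 87.7% | 83.6% | 83.7% | 82.0% | 80.9% |
| 0.8 | 0.3 | 0.025 | 80% | 91.7% | 86.5% | 86.7% | 83.8% | 81.8% |

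In the second row without shift, SE(β1) falls from 0.0143 to 0.0129. A Monte Carlo check (400 runs, binomial data, mixed model on empirical logits) gave 78% rising to 86% for the second row and 82% rising to 86% for the first.

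Over the wider assumed ranges, power reaches about 82–93% if site levels carry over unchanged (up to 96% with time coded 1 to 10), and about 80–90% with a shift of SD 0.3 to 0.8. A gain of 10 points would need the variance of β1 to fall by 1 − (2.802/3.242)² = 25%.

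**4. Balancing factors.** As main effects explaining 30% of intercept variance, they add about 0–4 points. With factor-by-time terms explaining 10%, 20% or 30% of slope variance, power is 80–83%, 81–86% or 81–89%. Four pre-quarters plus 20% of slope variance give about 86–94%, or 85–87% with a 0.5-logit shift.

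**5. What the model already does.** With no arm term on the intercept, the arms share a starting mean. Freeing it would lower power from 80% to about 54–80% in these settings, so part of the benefit of a common baseline is already taken.

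**The case against.** The strongest reply is that this is a condensed article. Covariates and run-in data are normally settled in a full analysis plan, and the equation, with exactly 48 patients at each of 54 sites, reads like the idealised model behind the power simulation. Nothing in it forbids adjustment. This stands to the extent that the point is a recommendation and not an error. It does not remove the point, because the article prints an explicit primary model and a better one is available from data it schedules.

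The second reply is that the history may be weak, and this limits the size of the gain:

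- The pre-randomisation year contains feedback and, for programs below target, the two-day academy. Both are meant to move outcomes.
- Randomised sites are selected for failing to achieve or sustain targets, so a flat, stable pre-period is doubtful.
- Quarterly collection from baseline is explicit only for Reach and Adoption.
- Table 3 defines access among patients prescribed MOUD, and Participants says 72% of the state's programs offer none, so early access data may be sparse.

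A reader might infer that the omission costs about 10 points of power. That figure needs chosen variances, full carry-over of site levels and 48 evaluable patients in every earlier quarter; the documents support none of these. A reader might also infer that the balancing factors share in that loss, but they are unnamed and do little as main effects on a slope test.

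For IMAT, a reader might scale a detectable effect of about 0.78 by √(1−r²) and obtain 0.74, 0.67 or 0.55 at r = 0.3, 0.5 or 0.7. That is a single-endpoint ANCOVA illustration at assumed correlations. The plan tests a difference in slopes, so those figures do not describe it.

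**Conclusion.** The printed primary model starts at randomisation and uses neither the earlier outcome data nor the balancing factors. It is valid but inefficient. From a calibrated 80%, the pre-randomisation quarters alone would add roughly 0 to 13 points (16 at the extreme), and about 1 to 4 with a 0.5-logit shift (up to 6 with time coded 1 to 10). Together with balancing factors that predict slopes, the gain is about 5 to 14 points.

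These ranges rest on assumed variance components, carry-over of site levels and numbers of evaluable early patients, none of which the article gives. The direction is sound; the size is not fixed by the document. The change is worth making because it costs little, not because the stated analysis is wrong.

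**What to change.** - **Primary model.** Prespecify each site's pre-randomisation level and its product with time as covariates, using 72-hour access where evaluable and otherwise Reach. Alternatively, add the earlier quarters with means common to both arms and a site-level shift at randomisation, so that a flat pre-period is not assumed. Keep the common starting mean.
- **Balancing factors.** Name them and include them with factor-by-time terms.
- **Access data.** State whether 72-hour access is collected quarterly from baseline.
- **IMAT.** Use the Phase 3 score as the baseline in the slope model. Reconcile this with Specific aim 2, which treats the same score as a mediator of the randomised condition although it is measured before randomisation.
- **Power.** Report the assumed variance components, so that any gain can be calculated.

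The cost is analysis wording and a rerun of the power simulation. No new data collection is needed if access is recorded before randomisation, or if Reach is used in its place.

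### The Aim 2 mediator, the Phase 3 IMAT score, is recorded before sites are randomized to internal or external facilitation, so this mediation path cannot show an effect of facilitation

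*Protocol article*

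**What the plan says.** Four statements in the protocol article bear on the timing.

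- **Randomization** (Implementation strategies): "All programs that do not achieve or sustain target outcome criteria by the end of Phase 3 (12 months from baseline) will be randomized" to NIATx-IF or NIATx-EF. Table 2 gives each facilitation strategy 9 months.
- **IMAT schedule** (Implementation outcomes, Aim 1): "the IMAT-SC will be assessed at baseline and at the end of each phase".
- **Use of the IMAT to route sites** (same section): "Three primary outcomes-Reach, Adoption, and Implementation (IMAT) serve as implementation targets to determine the stagewise path of participating organizations". The IMAT criterion is a Total Score of at least 3.
- **Mediation** (Data analysis, Specific aim 2): the analyses are set in the randomized component. "A core mediator of access to MOUD within 72-h of OUD diagnosis is the Phase 3 IMAT score". The text treats this score as an intermediate outcome and plans the indirect effect of strategy condition through it on the MOUD rate, by product of coefficients. The sentence introducing this step calls it moderation.

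**The concern.** A mediator has to be open to change by the exposure. Here the exposure is assignment to IF or EF, and the named mediator is a score taken at the end of the phase that precedes assignment. If that order is right, the first leg of the mediation path (assignment to mediator, the a-path) is zero by design. Any real effect of facilitation that works through better implementation quality would then appear in the direct effect.

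The conclusions drawn from this analysis are at stake. A null result would be read as evidence that implementation quality does not carry the facilitation effect, when the analysis could not have shown it. A positive result would be a chance difference between arms at baseline, reported as a mechanism.

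**Working it through.** **1. Order of events.** Sites are randomized at the end of Phase 3, month 12. The IMAT is taken at the end of each phase, so the Phase 3 IMAT is the month-12 score. It is also needed to decide whether a site has met target and so whether it is randomized. It must be known before assignment.

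**2. Check against the protocol's durations** (Implementation strategies; Specific aim 1).

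- Path 1: 6 active + 36 sustainment = 42 months. Path 5: 30 + 12 = 42 months.
- From randomization to the end: 42 − 12 = 30 months = 10 quarters, which matches the 10 outcome quarters in the IF-versus-EF model.

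The outcome series therefore starts at month 12, where the Phase 3 IMAT ends. Fig. 3 is not shown, but nothing in the text places this score after assignment.

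**3. The protocol's own figure for continuous measures such as the IMAT** (Power calculations): effect size 0.77 with 54 sites, or 0.81 with 49, at 80% power and 5% type I error (two-sided assumed).

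- n per arm = 2(1.96 + 0.842)² / d².
- d = 0.77 gives 27 per arm, or 54 sites, as stated; power at 27 per arm is 0.808.
- d = 0.81 gives 24 per arm, or 48 sites (stated 49).

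So 27 sites per arm and a shift of 0.77 SD are fair inputs below.

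**4. Chance imbalance in a baseline IMAT.** Under simple randomization, SE = √(1/27 + 1/27) = √(2/27) = 0.27 SD. The probability of an absolute imbalance above 0.2 SD is 2[1 − Φ(0.2/0.272)] = 46%. The protocol balances the groups before randomization. If the IMAT or its correlates are among the balancing factors, both figures are smaller.

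**5. Simulation of the product of coefficients.** 27 sites per arm, 20,000 runs, mediator = a × arm + noise, outcome = b × mediator + noise, unit variances. A linear outcome model stands in for the Poisson model. The b values are assumptions. The joint test requires both legs to be significant at 5%.

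| Mediator | b | Mean indirect effect | SD | a-path significant | Joint test significant |
|---|---|---|---|---|---|
| Before assignment (a = 0) | 0 | 0.00 | 0.04 | 4.8% | 0.2% |
| | 0.3 | 0.00 | 0.09 | 4.7% | 2.3% |
| | 0.5 | 0.00 | 0.14 | 5.0% | 4.5% |
| | 1.0 | 0.00 | 0.27 | 4.9% | 4.9% |
| After facilitation (a = 0.77) | 0.3 | 0.23 | 0.14 | 79% | 45% |
| | 0.5 | 0.38 | 0.18 | 79% | 73% |
| | 1.0 | 0.77 | 0.30 | 80% | 80% |

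With the mediator as named, the indirect effect averages zero whatever b is, and every significant result is a false positive. The zero follows from the timing and does not depend on b or on the linear model.

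**The case against.** **It is probably a wrong phase label.** The section describes the score as an intermediate outcome showing how fast implementation happens, which fits a measure taken after assignment. The same sentence says moderation while describing an indirect effect. A slip is plausible. But the section repeatedly names the Phase 3 score in the mediating role, and an analyst who follows the text would run an analysis that cannot work.

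**The Phase 3 IMAT has a legitimate use.** It does, as a baseline covariate or a moderator. The plan, however, describes an indirect effect by product of coefficients, which is mediation.

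**The damage is limited.** This stands. A reader might infer that all of Aim 2, or the IF-versus-EF comparison itself, is compromised. The documents do not support that. The CDI, ICS and ILS are also to be examined as mediators and are collected repeatedly, so waves after assignment exist. The Aim 1 comparison and the IMAT slope comparison do not use the Phase 3 IMAT as a mediator.

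**The 0.27 SD ignores balancing.** This also stands. It is the figure under simple randomization and should be read as an upper figure.

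**The outcome model.** A reader might infer a second error because the mediation is to be run "with a Poisson model for the MOUD rate outcome" while Aim 1 uses a binomial model with site random effects. The documents do not support this as a finding. The variance specification is not given, it is not clear that the MOUD rate is the same outcome as starting within 72 hours, and a different working model for a secondary analysis is not a contradiction.

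**Conclusion.** The plan is wrong as written on this point. The Phase 3 IMAT precedes assignment to IF or EF, so the true indirect effect through it is zero. What the analysis would estimate is chance imbalance multiplied by the association between baseline IMAT and outcome. The imbalance has a standard error of at most about 0.27 SD with 27 sites per arm, and less if balancing covers the IMAT.

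A reader might infer that the plan inflates false-positive mediation findings. It does not: the joint test stayed at or below about 5% in the simulation. The fault is that the analysis has no power for real mediation beyond that rate, so a misread null is the likelier harm.

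The timing rests on the text alone, because Fig. 3 is not shown, but the 42-month and 10-quarter arithmetic agrees with it. The power figures for a mediator measured after facilitation rest on an assumed 0.77 SD shift, assumed b values and a linear outcome model. The conclusion covers this one named mediator only.

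**What to change.** In Specific aim 2:

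1. Define the mediator as the first scheduled IMAT after each site's own IF or EF facilitation. A fixed end-of-Phase-4 score is tempting but would repeat the fault for some sites. Path 2 programs may re-enter at the end of Phase 4 having had only EMF and the Academy, so for any of these that then receive facilitation, that score is again a baseline value.
2. Enter the last IMAT before assignment (the Phase 3 score for most sites) as a baseline covariate in both the mediator and the outcome models.
3. Take the outcome from quarters after the mediator, so that exposure, mediator and outcome are in time order.
4. In the sentence introducing the indirect effect, replace moderation with mediation.

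**Cost.** No new data are needed, since IMAT assessments after each strategy are already scheduled. The price is fewer outcome quarters for this secondary analysis. If facilitation runs from month 12 to month 21, (42 − 21)/3 = 7 of 10 quarters remain. For a site whose facilitation ends at month 30, (42 − 30)/3 = 4 remain. The Phase 4 end date is not stated in the text, so these counts assume that the 9 months start at randomization. The Aim 1 analysis keeps all 10 quarters.
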